**Figure 2 figure2:**
[figure not shown]
Exercise prescription outline. Bars represents the exercise intensity (% of peak heart rate) at a given exercise session, and the dotted line represents the duration (minutes) at the prescribed exercise intensity in a given session.

In Figure 2, the intensity of each session is depicted by the colored bars as a percentage of the mean peak heart rate (HR_peak_) for the session. “Black sessions” are performed at 65% of HR_peak_ for 25-40 minutes (n=13), “light blue sessions” are performed at 75% of HR_peak_ for 30 minutes (n=17), and “green sessions” are performed at 83.5% of HR_peak_ for 30 minutes (n=2). “Dark blue sessions” are performed as three to five 4-minute intervals at 93.5% of HR_peak_ with 3 minutes active rest (brisk walking) between intervals (n=16), and “purple sessions” are performed as two to four 8-minute intervals at 88% of HR_peak_ with 4 minutes active rest (brisk walking) between intervals (n=8). Orange bars represent sessions where the CPET exercise protocol is repeated and are conducted every fourth week (n=4). The treadmill speed and grade at voluntary exhaustion at the CPET protocol sessions will be recorded and used to monitor and report training progression throughout the intervention.

All exercise sessions will be supervised by an instructor at the participant’s local gym. The instructors make sure that the planned exercise sessions are performed and adjust the sessions if necessary. They will also register any deviation from the exercise prescription and report the reason for any adjustment following metrics suggested by Nilsen et al [55]. Adverse events will be reported to the study staff. To increase exercise adherence and educate the instructors, the instructors will be encouraged to undergo a series of web-based seminars. They will be introduced to the rationale for the study, behavior change principles, and how to identify facilitators and barriers to exercise.

BCS randomized to the control group will be encouraged to maintain their current activity level at the time of randomization.

### Statistical Analysis

The sample size calculation was based on the primary outcome VO_2peak_, using a mean change of 3.6 (SD 7.2) mL/kg/minute, from a comparable intervention by Adams et al [23]. With a significance level of 5% and a power of 90% (to compensate for using published results from a single study in our sample size calculation), 63 BCS are needed in each group. To allow for a dropout rate of 7 participants (10%), a total of 70 BCS are included in each group. The same number of participants are included in the reference group. The primary and secondary outcomes are analyzed by generalized linear mixed models. Baseline outcomes in women with and without previous cancer are compared by a 2-sample *t* test.

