### Randomization

BCS are block randomized with a 1:1 allocation ratio to the exercise group or to the control group. Due to the strict eligibility criteria, no additional stratification factors are included. A random sequence of study IDs was made by a random number generator prior to inclusion of the first participant. The allocation sequence is concealed from the study personnel involved in baseline assessment until the baseline assessments are completed.

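### The sample size of 63 per arm gives about 80% power on the stated inputs, not the stated 90%, so the claimed reserve is absent

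*Protocol article*

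**What the plan says.** The Statistical Analysis section of the protocol article gives a complete calculation for the primary outcome: "The sample size calculation was based on the primary outcome VO_2peak" (treadmill peak oxygen uptake).

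- **Effect and spread:** "using a mean change of 3.6 (SD 7.2) mL/kg/minute", taken from one published exercise trial.
- **Error rates, and the purpose of the power level:** "With a significance level of 5% and a power of 90% (to compensate for using published results from a single study". The section does not say whether the test is one- or two-sided.
- **Result:** "63 BCS are needed in each group".
- **Dropout:** "To allow for a dropout rate of 7 participants (10%), a total of 70 BCS are included in each group".

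The comparison is between two independent arms. The Design section sets exercise against standard care, and under Randomization "BCS are block randomized with a 1:1 allocation ratio". The section gives no baseline to follow-up correlation and no covariate adjustment as part of the sizing.

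**The concern.** A difference of half a standard deviation at two-sided 5% significance and 80% power is a familiar case, and its answer is 63 per group. The same 63 appears here against 90% power, which should need about a third more women.

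The label matters because the protocol gives the 90% a job: it is the safeguard against drawing the effect and SD from a single study. By the Introduction's own description, that study gave 12 weeks of supervised high-intensity exercise to testicular cancer survivors. This trial gives five months of mixed-intensity exercise to long-term breast cancer survivors, so a margin against wrong inputs is worth having. If the margin is not there, the chance of missing a true 3.6 mL/kg/min effect is about one in five rather than one in ten. A non-significant primary result would then be read as stronger evidence against that effect than the design supports.

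**Working it through.** **Inputs** (Statistical Analysis, Randomization): difference 3.6, SD 7.2, significance 5%, power 90%, 1:1 allocation, 63 evaluable per arm, 10% dropout. Two-sided testing is assumed first because sidedness is not stated.

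**Standardised effect.** d = 3.6 / 7.2 = 0.50.

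**Attempt to reproduce 63 at 90% power.** Normal formula, per arm: n = 2(z for two-sided 5% + z for power)² / d².

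- 90% power: 2 × (1.960 + 1.282)² / 0.25 = 84.1, so 85. The t test gives 85.03, so 86.
- 80% power: 2 × (1.960 + 0.842)² / 0.25 = 62.8, so 63. The t test gives 63.8, so 64.

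The stated 63 does not reproduce at 90%. It matches the 80% answer from the normal formula.

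**Dropout step.** 63 / (1 − 0.10) = 70. This reproduces and is not in question.

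**Power at the planned sizes (two-sided 5%, d = 0.50)**

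| Evaluable per arm | Normal | t test |
|---|---|---|
| 63 | 80.1% | 79.5% |
| 70 (no dropout) | 84.1% | 83.6% |
| 86 | – | 90.3% |

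For example, at 63 per arm: 0.5 × √(63/2) = 2.806, 2.806 − 1.960 = 0.846, and the normal probability below 0.846 is 0.801.

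**What 63 per arm does give at 90% power.** With SD 7.2, the detectable difference is 7.2 × (1.960 + 1.282) × √(2/63) = 4.16 (normal) or 4.19 (t test). With the difference held at 3.6, the SD would have to be about 6.2.

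**What 90% would have needed after dropout.** 85 / 0.9 or 86 / 0.9 gives 95 or 96 per arm, that is 190 to 192 women against the 140 planned.

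**If the single-study input is optimistic.** With a true difference of 3.0 (an illustrative assumption) and SD 7.2, t-test power is 64% at 63 per arm. It would be about 78% at the 86 per arm that 90% power requires.

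**Other readings tried**

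- *One-sided 5%:* 90% needs 68.5, so 69 (normal), or 69.2, so 70 (t test). Power at 63 is 87.7% (normal) or 87.4% (t test). It does pass 90% at 70 per arm (90.3%, t test), but the protocol attaches 90% to 63 and presents 70 as the number that allows for dropout.
- *Paired or one-sample test:* 44 women in total for 90% power. This does not match, and it is not the randomised comparison.
- *Baseline-adjusted analysis, 7.2 read as a cross-sectional SD:* with correlation 0.5, n = 84.06 × (1 − 0.25) = 63.04, so 64.
- *Change score, 7.2 read as a cross-sectional SD:* a correlation of about 0.63 would be needed to reach 63.

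**The case against.** The best reply accepts that the printed numbers disagree but disputes which one is wrong. An SD of 6.2 with 90% power gives 2 × (1.960 + 1.282)² × (6.2/3.6)² = 62.3, which also rounds up to 63, so a one-digit misprint in the SD would fit. Reading 7.2 as a cross-sectional SD with a baseline correlation of 0.5 also lands at 63.04. In addition, the article names generalized linear mixed models for the primary outcome. If 7.2 is cross-sectional and the model uses baseline, power at 63 per arm would be about 83%, 90% and 97% at correlations of 0.3, 0.5 and 0.7. Finally, recruitment is over, and the estimate with its confidence interval will carry the evidence whatever the planned power was.

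Part of this stands. The source study cannot be seen, the origin of the slip cannot be proved, and the analysis may achieve more than 80% in practice. It does not rescue the statement. Nothing in the article supports an SD of 6.2. The SD is attached to a mean change, and no correlation or adjustment is given, so a further reduction for baseline has no basis in the text. If the sponsor did rely on such an input, the sentence still needs correction, because the inputs it gives do not lead to its result. The confidence interval limits the harm from misreading a null result but does not make the stated power true.

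**Conclusion.** The concern holds: the power statement is wrong as written. On the protocol's own 3.6 with SD 7.2, two arms at 1:1 and two-sided 5%, 63 evaluable women per arm give about 80% power, not 90%. The type II error is about 20% rather than 10%. The shortfall against the requirement is 22 (normal) or 23 (t test) evaluable women per arm, roughly a quarter of the number needed. Even with no dropout, power is about 84%. The reserve claimed against single-study inputs is therefore not in the calculation.

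This rests on reading 7.2 as the SD of the quantity compared, which is how the article presents it, and on two-sided testing. The one-sided alternative also falls short at 63.

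**What to change.** Do not enrol more women; inclusion closed in August 2022.

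1. Correct the power statement along these lines: 63 evaluable women per arm give 80% power (about 84% if all 70 per arm are evaluable) to detect a difference of 3.6 mL/kg/min with SD 7.2 at two-sided 5% significance, and 90% power for a difference of about 4.2 mL/kg/min.
2. Delete the claim that 90% power compensates for taking the inputs from a single study.
3. Carry the corrected figures into the results paper.

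If the sponsor's records show that a different SD or a baseline correlation was used, that input should be stated and the power given for it.

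The cost is one corrected sentence and a less favourable stated power, with no extra participants or data.

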### Aims and Hypothesis

The primary aim of this study is to examine the effect of aerobic exercise on CRF in anthracycline-treated long-term BCS compared to standard care. Secondary aims are to examine the effects of exercise training on limiting factors for CRF, CV risk factors, and health-related patient-reported outcomes (PROMs) compared to standard care, and to compare baseline values and effects of exercise training between BCS and similar-aged women without prior cancer. Tertiary aims are to investigate long-term effects of the intervention on CRF, CV risk factors, and health-related outcomes 24 months post intervention. We hypothesize that aerobic exercise will improve CRF.

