### Participants

#### BCS Group

BCS are invited to participate if diagnosed with human epidermal growth factor receptor 2

–negative breast cancer stage I-III between 2008 and 2012 (ie, 8-14 years after diagnosis), aged 60 years or younger at the time of diagnosis, and received the anthracycline epirubicin as part of their adjuvant therapy. All eligibility criteria are listed in Textbox 1.

Eligibility criteria for breast cancer survivors in the CAUSE (Cardiovascular Survivors Exercise) trial.Inclusion criteria:Adjuvant treatment with epirubicinBreast cancer diagnosis between 2008 and 2012Exercises ≤90 minutes per weekPhysicians’ approval of participationExclusion criteria:Stage IV breast cancer at diagnosisTreatment with trastuzumabRecurrence of breast cancerPresence of other malignancies (except for basal cell carcinomas)Former major cardiac surgeryPresence of a pacemakerChronic atrial fibrillationRecent or uncontrolled cardiovascular diseaseAny physical or mental condition restricting adherence to study procedures (by self-evaluation)

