#### Noncancer Reference Group

Participants in the noncancer reference group are women without a history of cancer who otherwise meet the eligibility criteria listed in Textbox 1.

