### Recruitment

Women who were diagnosed with breast cancer stage I-III between 2008 and 2012, and live within reasonable distance from Oslo, are identified from the Cancer Registry of Norway. An invitation with study information is sent by mail to all candidates. Thereafter, the study personnel contact the candidates by phone to screen for eligibility and provide additional information. Candidates who meet the eligibility criteria and are willing to participate are then invited to baseline assessments.

Participants for the noncancer reference group are recruited in 2 steps. First, BCS randomized to the exercise group are encouraged to invite a similar-aged friend or relative to participate in the noncancer reference group. The remaining participants in the noncancer reference group are recruited through advertisements in news media and through appropriate social media channels. Interested candidates who meet the eligibility criteria are included.

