		**Unhealthy lifestyle**			
			Level of physical activity	ActiGraph GT3X+	T_1_, T_2_, T_4_
			Smoking status	HUNT-4^h^	T_1_, T_2_, T_4_

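### The baseline comparison of women with and without previous cancer is fixed as an unadjusted two-sample t test, although the reference group is neither randomised nor stated to be matched, so a residual age difference would pass as an effect of cancer therapy or hide one

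*Protocol article*

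**What the plan says.** All references are to the protocol article.

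- **Aim.** Aims and Hypothesis lists among the secondary aims "to compare baseline values and effects of exercise training between BCS and similar-aged women without prior cancer".
- **Method.** Statistical Analysis: "Baseline outcomes in women with and without previous cancer are compared by a 2-sample" *t* test. No covariate, matching or restriction is mentioned. The same section assigns primary and secondary outcomes to generalized linear mixed models, so the *t* test concerns baseline only.
- **Eligibility of the reference group.** Noncancer Reference Group: "women without a history of cancer who otherwise meet the eligibility criteria listed in Textbox 1".
- **Age rule.** BCS Group requires survivors to be "aged 60 years or younger at the time of diagnosis" and adds: "All eligibility criteria are listed in Textbox 1". Textbox 1 as shown has no age criterion.
- **Recruitment.** Survivors are identified from the Cancer Registry of Norway. For the reference group, "BCS randomized to the exercise group are encouraged to invite a similar-aged friend or relative to participate in the noncancer reference group". The remaining reference women come through news media advertisements and social media.
- **Intended reading.** The Discussion says the reference group allows a direct comparison of baseline levels between women exposed and unexposed to cancer therapy. The safeguard it names is a similar physical activity criterion in both groups.

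**The concern.** Only the survivors are randomised, and only between exercise and standard care. Cancer history is an observed characteristic, so the cancer versus noncancer comparison has no design protection against confounding beyond the shared eligibility criteria and the intention to recruit women of similar age.

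That intention has no operational form in the article. The only numerical age limit is tied to the date of a diagnosis that reference women never had, and the list they are referred to contains no age criterion. The shared activity limit does nothing about age or recruitment channel. The Discussion itself presents registry recruitment of survivors, rather than media advertising, as a way to reduce selection bias; yet media advertising supplies part of the reference group.

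An unadjusted *t* test attributes the whole mean difference to cancer history. If reference women are on average younger, and fitness declines with age, survivors look impaired even when therapy had no late effect. If reference women are older, a real deficit shrinks or disappears. Either way a secondary aim is answered wrongly, and the answer is meant to be read as exposed versus unexposed.

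The method is stated, so this is an unsuitable choice and not a detail left to an analysis plan.

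**Working it through.** The plan gives no sample size, power or expected difference for this comparison, so there is no figure of its own to reproduce. The check asks how an unadjusted test behaves when there is no true effect of cancer history but the groups differ in mean age.

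**Inputs from the article**
- Planned group sizes: 70 + 70 = 140 survivors and 70 reference women (Statistical Analysis). The 209 women actually included are one fewer than the planned 210, which is immaterial here.
- SD 7.2 mL/kg/min (Statistical Analysis). This is quoted as the SD of a *change*; no baseline SD is given.

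**Assumed inputs**
- Baseline SD of VO2peak: 5, 6 or 7.2 mL/kg/min.
- Fall in VO2peak per year of age: 0.2 to 0.5 mL/kg/min.
- Difference in mean age between groups: 0, 1, 2 or 3 years.
- Two-sided 5% test, normal approximation.

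**Step 1: standard error.** SE = SD × √(1/140 + 1/70) = SD × √0.021429 = SD × 0.1464.
- SD 5: SE = 0.732
- SD 6: SE = 0.878
- SD 7.2: SE = 1.054

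**Step 2: bias.** b = slope × age gap. For example, 0.3 × 3 = 0.9 mL/kg/min.

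**Step 3: false-positive rate.** P = Φ(b/SE − 1.96) + Φ(−b/SE − 1.96). With b = 0.9 and SD 7.2, b/SE = 0.854 and P = 13.7%.

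Range over SD 7.2 (lower figure) to SD 5 (higher figure):

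| Slope per year | gap 0 | gap 1 year | gap 2 years | gap 3 years |
|---|---|---|---|---|
| 0.2 | 5.0% | 5.4–5.9% | 6.7–8.5% | 8.8–13.0% |
| 0.3 | 5.0% | 5.9–6.9% | 8.8–13.0% | 13.7–23.3% |
| 0.4 | 5.0% | 6.7–8.5% | 11.8–19.4% | 20.7–37.4% |
| 0.5 | 5.0% | 7.6–10.5% | 15.8–27.7% | 29.6–53.6% |

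With slopes of 0.2 to 0.4, a 1-year gap gives 5.4 to 8.5%, and gaps of 2 to 3 years give 6.7 to 37.4%. A slope of 0.5 takes the top of the 3-year range to 53.6%.

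**Step 4: friend and relative pairs.** Suppose m of the 70 reference women are each correlated ρ with one survivor. The variance of the mean difference is then SD² × [1/140 + 1/70 − 2mρ/(140 × 70)].
- m = 20, ρ = 0.2: 0.020612/0.021429 = 0.96 of the variance the *t* test assumes; actual error rate 4.6%.
- m = 70, ρ = 0.5: 0.014286/0.021429 = 0.67; actual error rate 1.6%.

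Positive correlation across the groups therefore makes the test conservative.

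**The case against.** **The article does restrict age informally.** Similar-aged describes the whole reference group in the Abstract, Aims and Design, not only invited friends. The activity limit and the applicable exclusions are shared, and how similar age was applied in numbers may stand in the full protocol. This has force: one cannot conclude that age was uncontrolled or that a gap exists. The oldest possible survivor at entry, 60 + 14 = 74 years, is an individual extreme and says nothing about group means. What remains is that the stated analysis has no protection if recruitment left a gap.

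**The percentages are hypothetical.** This stands. Gap, direction and slope are assumed, and 7.2 is the SD of a change standing in for a baseline SD. The table shows sensitivity, not expected bias.

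**Pairing.** A reader might infer that friend and relative pairs make the *t* test anticonservative or biased. They do not: positive correlation across the groups lowers the true variance, so ignoring it costs precision and nothing else. Only exercise-group women are asked to invite someone, so pairing is partial in any case, and the article does not say that links between inviter and invitee are recorded.

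**Outcome types.** A reader might also infer that smoking status or skewed biomarkers will be *t*-tested, since the sentence is unqualified. That reads a one-sentence summary too literally. Handling of categorical outcomes and transformations belongs in an analysis plan, which is not shown.

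**Adjustment is not a full cure.** Adjusting for age and education does not remove the difference between registry-identified survivors and invited or self-selected volunteers. This limits what the comparison can claim, but is no argument for leaving age unadjusted.

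**Conclusion.** The point holds in a limited form. An unadjusted two-sample *t* test is a poor choice for a non-randomised comparison that is a stated secondary aim and is to be read as exposed versus unexposed to cancer therapy.

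The consequence depends on an age gap that the article does not report. A gap of about 1 year would do little harm unless the age slope is steep. At 2 to 3 years the nominal 5% error rate is materially exceeded over most of the assumed range, and a gap in the other direction could conceal a true deficit. The article does not show that such a gap occurred.

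The planned randomised comparison of exercise with standard care is untouched. So is the comparison of training effects between survivors and reference women as far as this sentence goes, because the *t* test is named for baseline values only. The point merits a change but does not threaten the trial's main result.

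**What to change.** - **Main analysis.** Replace the *t* test by regression of each baseline outcome on group (previous cancer or not), adjusted for age at baseline and education level. Education is among the sociodemographic variables listed under Patient-Reported Outcomes.
- **Second.** Report the unadjusted difference beside it, with the age distribution of both groups, so that readers can see how much age matters.
- **Wording.** Describe the result as an observational association with previous cancer, and state that recruitment channels differed and that adjustment does not remove volunteer selection.
- **Optional.** If inviter and invitee links were recorded, model the pairs to recover some precision. If not, leave them out; ignoring them is conservative.

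The cost is a change of wording in the analysis plan and slightly more analysis work. No further participants, visits or measurements are needed, and the change remains possible although inclusion has closed.

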## Results

The inclusion started in October 2020 and was completed in August 2022. A total of 209 participants were included and postintervention assessments (T_2_) were completed in January 2023. The 24-month follow-up (T_4_) will be completed in February 2025.

## Discussion

Exercise training has previously been shown to improve CRF [20], but there is a paucity of studies investigating the effects of exercise training on other CVD risk factors following cancer treatment [22]. The CAUSE-trial will provide a novel understanding of the potential of exercise training to improve CRF, CV risk profile, and self-reported health-related outcomes in long-term BCS. Since impaired CRF has been reported in cancer survivors [9,10], it is pivotal to understand how previous exposure to cancer treatment modulates the effects of exercise. We hypothesize that previous exposure to cancer treatment, even 10 years ago, would have an impact on the expected results from exercise training. This study will expand on the current literature by thoroughly evaluating exercise effects across the entire cardiopulmonary-muscle axis, and by including an exercise group without a history of cancer. This allows us to directly compare baseline levels and intervention effects between women previously exposed to cancer therapy and unexposed women, and to identify potential bottlenecks to physiological adaptation to exercise training.

As with CRF, the positive effects of exercise training on several PROMs have been reported previously, but the existing literature is mainly limited to effects of exercise training during or shortly after cancer treatment. This is concerning, since approximately 30% of BCS still report chronic fatigue up to 10 years after completing treatment. Results from exercise training performed during or immediately after cancer treatment cannot necessarily be extrapolated to long-term survivors as the mechanisms behind chronic fatigue might differ from the more acute complaints. Although positive effects of exercise training on quality of life already have been demonstrated, less is known about the impact of exercise on other late effects in long-term BCS, such as mental distress, disturbed body image, pain, and sexual health challenges.

One of the major strengths of this study is the solid multidisciplinary constellation of the research group. Our group includes sports physiologists, cardiologists, oncologists, and behavioral scientists. This is also reflected by the list of study outcomes (Table 1) ranging from cardiopulmonary function to skeletal muscle cell function and morphology, and quality of life. Combined with a well-monitored, individually tailored exercise intervention, inclusion of a noncancer reference group, large study cohorts, and longtime follow-up, this will allow for exploring interactions across disciplines.

Our study design has some potential limitations. As with any lifestyle intervention study, we risk recruiting the most motivated and physically active participants, which may compromise the external validity of our results. We aim to reduce this risk of selection bias by recruiting BCS through the Cancer Registry of Norway rather than through media advertisements. Importantly, we use similar exclusion criteria for physical activity levels between cancer survivors and the reference groups, which enable us to identify any modifying effects of previous cancer treatment. Unfortunately, this study lacks completely blinded assessors. As an effort to reduce the influence of known group allocation, assessors will not know the baseline values of participants prior to the postintervention CPET. Furthermore, study staff will use similar feedback and encouragement during all tests. As in all clinical trials, poor intervention adherence and dropouts are major concerns. We attempt to counteract this by using instructors trained in motivational feedback. The knowledge acquired from this study will help to inform future cancer care guidelines.

